### Cost-effectiveness analysis

A cost-effectiveness analysis will be conducted alongside the RCT described above. The analysis will take the perspective of the NHS and Personal and Social Services, consistent with the National Institute for Care Excellence (NICE). A within-trial analysis will be conducted initially examining the costs and outcomes observed within the trial period. We will extend the time horizon if there are substantial differences between the groups in re-admission rates and/or adverse events at the final follow-up (90 days). Where extrapolation beyond one year is conducted, discounting will be applied at recommended rates (currently 3.5% per annum on costs and effects). The extrapolated analysis to a longer time horizon will be the primary analysis.

We propose to assess the cost-effectiveness of the YCNY intervention by collecting data on the costs of the intervention, utilisation of health care, and key patient outcomes.

Administered to patients or their proxy:The EQ5D-5L will be administered at baseline and at the three post-discharge follow-ups (T1, T2, and T3).The number of presentations to healthcare professionals, e.g. outpatient appointments, day case appointments, accident and unplanned attendances and use of community services.

From routine data:The number and duration of readmissions to the hospital trust following the index admission

From published literature:Unit costs of health care

To estimate the cost of the intervention:The costs associated with producing the booklet, and the instructions to patients document (a per-participant cost).The costs associated with developing the patient film (a one-off cost).The costs associated with staff implementing the intervention i.e. introducing the intervention and in applying the instructions to the patient’s documents. We will record which staff are involved, their grade, and, if possible, how many minutes of their time it takes (a per-participant cost).

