### Patient population and sample size

Based on findings of similar interventions targeting readmission in a systematic review by Leppin and colleagues [12] and an underlying risk of readmissions of 18% for older patients (based on local hospital statistics), we anticipate an absolute difference in readmission at 30 days between control and intervention wards of between 4% and 6%. We therefore plan for a 4.5% reduction in readmissions at 30 days. Assuming 80% power, alpha = 0.05, intraclass correlation coefficient ) = 0.01, average cluster size = 140 (30–40 older people discharged per month from 40 wards for 5 months) and 10% attrition rate, 5440 participants are needed.

It would not be efficient to design the study to recruit and consent 5440 patients. Instead, we will use routinely collected data to explore readmission rates and include individual data collection of a nested cohort of participants within this larger sample. We will power the nested individual data collection cohort for our secondary outcome of quality of transitions. This will be measured by the Partners At Care Transitions Measure (PACT-M) [30] which produces an overall score between 0 and 67. Assuming a mean difference of 2.7 points, which equates to a reduction of around half an adverse event and a standard deviation of 9 (based on data from the feasibility cRCT), 170 patients per group are required (80% power, alpha = 0.05). Allowing for clustering this would increase to (assuming equal clusters of 25 patients and an ICC of 0.05) 374 patients per group. Allowing for 25% attrition (based on projected results from our feasibility study) we will recruit 500 patients per group (1000 total) which would require 40 clusters. We assume an ICC of 0.05 in the absence of published data indicating the most appropriate ICC for this setting and particular outcome.

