### Statistical analysis

A CONSORT diagram will document the flow of wards and participants through each stage of the trial.

Readmission rates will be summarised descriptively at each time-point by treatment group and overall. The primary analysis will use a repeated-measures mixed model to compare the treatment groups. This will account for the hierarchical nature of the data by including Trust and ward as random effects and the repeated measurements from participants will be modelled by the covariance structure. The outcome will be readmission (yes/no) at 30, 60 and 90 days and the model will include important baseline covariates (e.g. minimisation factors), treatment group and time as fixed effects. An interaction term assessing whether the difference between the treatment groups changes over time will also be included in the model.

The primary analysis will compare the groups at 30 days. Secondary analyses will compare the two groups at 60 and 90 days post-discharge

Detailed statistical methods will be outlined in a separate Statistical Analysis Plan.

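### Which cost-effectiveness analysis is primary depends on the trial's own 90-day results, because the extrapolation named primary is run only if the observed differences are substantial

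*Protocol article*

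**What the plan says.** Three statements in the Cost-effectiveness analysis section of the protocol article bear on the point, in this order.

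- The starting point is unconditional: "A within-trial analysis will be conducted initially examining the costs and outcomes observed within the trial period".
- The longer horizon is conditional: "We will extend the time horizon if there are substantial differences between the groups in re-admission rates and/or adverse events", assessed at the last follow-up, 90 days after discharge.
- Primary status is then given without condition: "The extrapolated analysis to a longer time horizon will be the primary analysis".

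On the length of the horizon the section says only this: "Where extrapolation beyond one year is conducted, discounting will be applied at recommended rates". No sentence says which analysis is primary if the condition is not met. The abstract and the study aims and objectives make cost-effectiveness an unconditional question of the trial, alongside effectiveness.

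**The concern.** The second and third statements do not fit together. An analysis that may or may not be run is named as the primary one. The condition for running it is the trial's own outcome data, on either of two endpoints and in either direction.

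A base case chosen after the results are seen is not pre-specified. The selection is also lopsided. A large observed difference becomes the input to a model that carries it beyond 90 days in the headline result. A small observed difference stays within 90 days. Large differences that arise by chance pass the same filter as real ones. At stake is the credibility of the headline answer to one of the trial's two main questions. The 30-day readmission comparison in the Statistical analysis section does not depend on this rule.

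**Working it through.** **1. The rule read literally.** No figure is attached to it, so the check is one of logic.

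| Observed 90-day differences | Within-trial analysis | Extrapolation | Primary economic analysis |
|---|---|---|---|
| Not substantial | done | not done | none named; within-trial only by inference |
| Substantial | done | done | extrapolation |

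A cost-effectiveness estimate exists in both rows. What changes between them is which analysis is primary, and the observed data decide that.

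**2. Inputs for an illustration.** From the Patient population and sample size and Randomisation sections: control risk 18% at 30 days; planned effect ("We therefore plan for a 4.5% reduction in readmissions at 30 days"), hence 13.5%; ICC 0.01; average cluster size 140; 10% attrition; N = 5440; 40 wards, 1:1. A two-sided 0.05 level is assumed.

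The plan's own sample size reproduces from these inputs:

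- Per arm, unpooled: (1.96 + 0.8416)² × (0.18 × 0.82 + 0.135 × 0.865) / 0.045² = 1024.7.
- Design effect: 1 + 139 × 0.01 = 2.39.
- Total: 2 × 1024.7 × 2.39 / 0.9 = 5442, against 5440 stated. The pooled formula gives 1028 per arm and 5460.

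**3. How far chance can decide whether the trigger is met.** The article gives no 90-day readmission rate, so 18% to 35% is assumed. With 5440/40 = 136 patients per ward, the design effect is 1 + 135 × 0.01 = 2.35, and SE = √(p(1 − p) × 4/5440 × 2.35). For p = 0.18 this is √(0.1476 × 0.000735 × 2.35) = 0.0160. The cut-offs are assumptions too, since the article states none. Each probability is for an observed difference of at least that size in either direction, by normal approximation.

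| Assumed 90-day rate | SE (points) | No true effect: ≥2 points | ≥3 points | ≥4.5 points | True 2-point effect: ≥3 points |
|---|---|---|---|---|---|
| 18% | 1.6 | 0.210 | 0.060 | 0.005 | 0.266 |
| 25% | 1.8 | 0.267 | 0.096 | 0.012 | 0.292 |
| 30% | 1.9 | 0.294 | 0.115 | 0.018 | 0.304 |
| 35% | 2.0 | 0.313 | 0.130 | 0.023 | 0.313 |

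Using 4896 patients (5440 × 0.9) instead moves the SE only to 1.63 to 2.03 points. The table covers readmissions alone; the adverse-event route adds a further, unquantified chance of meeting the trigger.

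**4. What selection does and does not do to the estimate.** Suppose, for illustration only, that the trigger means nominal significance in favour of YCNY, with the SE the plan implies at 30 days. With 4896/40 = 122.4 analysed per ward and 2448 per arm, SE = √(0.264375 × (1 + 121.4 × 0.01) / 2448) = 1.546 points, and the cut-off is 1.96 × 1.546 = 3.03 points. If the true reduction is 2 points:

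- The trigger is met with probability 0.25, and the mean observed reduction is then 3.96 points.
- Otherwise (probability 0.75) the mean observed reduction is 1.34 points.
- Weighted: 0.2525 × 3.96 + 0.7475 × 1.34 = 2.0 points, the truth.

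So the trigger leaves the observed estimate itself unchanged and, on average, unbiased. It separates the results: those averaging 3.96 points are projected in the headline analysis, and those averaging 1.34 are not. At the planned 4.5-point effect the separation matters less: the trigger is met 83% of the time and the conditional mean exceeds the truth by a factor of only 1.1.

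**The case against.** The strongest defence reads the paragraph in sequence: do the within-trial analysis, extend it if differences persist, and treat the longer horizon as primary where it has been extended. On that reading nothing conflicts and only a clause is missing, one confirming that the within-trial analysis is otherwise primary. There is also a reason for the condition: if the groups hardly differ at 90 days, there is little effect to project. The article condenses a fuller protocol, and a threshold or horizon length may be set there or in an economic analysis plan. The Statistical analysis section does announce a further document ("Detailed statistical methods will be outlined in a separate Statistical Analysis Plan"), although the economic section itself refers to none.

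Much of this stands. Extending a horizon is legitimate, and the missing definition of *substantial* and the missing horizon length are not held against the article. What remains is that, even on the kindest reading, the primary analysis is settled after the results are seen. A definition elsewhere would make the trigger reproducible but would still select on the outcome.

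A reader might infer two stronger things. One is that the trial may end with no economic result, or cannot answer its cost-effectiveness objective. The text does not support that, because the within-trial analysis is promised in all cases. The other is that the gap between 3.96 and 2 points (a factor of 2.0) measures bias in the reported cost-effectiveness. It does not. It is a mean conditional on an assumed one-directional significance trigger, it uses a 30-day SE although the rule is applied at 90 days, and the same conditional exaggeration would appear in the within-trial analysis among results selected in the same way.

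**Conclusion.** The point holds in a limited form. The article states a results-dependent trigger and also states that the analysis behind it is primary, with no fallback. A cost-effectiveness result will exist, but its base case is picked by the data, and only large observed differences reach the longer-horizon headline.

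The size of the effect on reported cost-effectiveness cannot be derived from the article, and no multiplier should be attached to it. What can be shown, under assumed 90-day rates of 18% to 35% and ICC 0.01, is that the choice is sensitive to chance. With no true effect, a 2-point cut-off would be passed with probability about 0.21 to 0.31 and a 3-point cut-off about 0.06 to 0.13. With a true 2-point effect, a 3-point cut-off would be passed only about 27% to 31% of the time.

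This should be fixed, but it is confined to the economic evaluation. The 30-day primary comparison, the 60- and 90-day readmission analyses, the sample size and the data collected are untouched.

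**What to change.** Name one base-case economic analysis in advance, whatever the results. Either option settles it:

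- Make the 90-day within-trial analysis primary, with the extrapolation as a pre-specified secondary or scenario analysis. The downside is a shorter horizon for the headline result.
- Keep the extrapolation primary, run it unconditionally, and delete the clause that makes it depend on substantial differences. Its horizon should then be fixed before the data are seen.

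Report both analyses in either case. The change is about two sentences in the protocol or health-economics plan and needs no new data. If the choice is made after the 90-day results are known, the report should say so.

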### Embedded process evaluation

The embedded process evaluation aims to assess the fidelity of the intervention, exploring contextual factors that shape the delivery of YCNY and how it is used in practice.

Data generated will be used to interpret trial outcomes and optimise the intervention and implementation package for future use.

Guidance on the design of process evaluations [42] proposes that evaluations of complex interventions should explore: context, implementation, and mechanisms of impact. In keeping with this guidance, the YCNY process evaluation has three key objectives (see Fig. 3) aiming to investigate:*Context* within which YCNY is delivered (treatment wards) and factors that may impact trial outcomes (e.g. contamination)*Implementation* of the intervention, specifically exploring what is delivered, how, and by whom*Mechanisms of impact*, specifically how the intervention is received and used by key stakeholders, especially patients and staff

**Fig. 3 Fig3:**
[figure not shown]
Key objectives of the YCNY process evaluation

Data about site/ward set-up and early intervention delivery will be generated through structured reflections by researchers. These will be used to capture researcher perspectives on-site engagement, barriers and facilitators to intervention implementation and delivery, and other details which they feel may influence outcomes.

### Mechanisms of impact data

A more detailed ethnographic study will be conducted on approximately eight intervention wards. This will include:Staff experience interviews: approximately 24 semi-structured interviews will be conducted with staff involved in delivering the intervention, including the YCNY facilitators;Observation of care with staff and patients/carers to see how people interact with the intervention and with one another in light of the intervention as usual care;Semi-structured interviews with approximately 24–30 patients and their carers about their experiences of and perspectives on the YCNY intervention and the care they received whilst in hospital. We will also ask to look at and analyse YCNY booklets that patients have used.

All staff, patients and carers invited to take part in the ethnographic study will be provided with an information sheet and the opportunity to ask questions with time to consider participation. Consent will be documented for those who agree to take part.

### Data analysis within process evaluation

Data from the interviews, observations and intervention booklets will be analysed using a ‘pen portrait’ method [43]. Pen portraits are used to synthesise data across different sources. All data related to a ward will be drawn together to describe ward characteristics, how the intervention was implemented and delivered, how people (staff and patients) engaged with it, contextual factors which shaped its delivery/use, and patients’ experiences and views of it.

### Trial organisation and administration

The cRCT is being conducted as part of a five-and-a-half-year Programme Grant for Applied Health Research (RP-PG-1214-20017) funded by the National Institute for Health and Care Research. The trial is sponsored by Bradford Teaching Hospitals NHS Foundation Trust and is coordinated by YQSR at the Bradford Institute for Health Research, and YTU at the University of York.

Approvals were gained from the North East - Newcastle & North Tyneside 2 Research Ethics Committee, Confidentiality Advisory Group, and the Health Research Authority prior to starting the study (REC reference 20/NE/0020, CAG reference 21/CAG/0054). Local NHS capability and capacity approvals were granted by all participating NHS Trusts. Any amendments to the protocol will be submitted for the required regulatory approval. The study is registered on the UK Clinical Research Network Study Portfolio (44559) and the ISTCRN (ISRCTN17062524).

### Patient and public involvement

The PACT programme grant has an active patient panel who have been involved in co-designing the YCNY intervention and have advised and supported the development of study procedures and documents. Panel members were involved in the intervention iteration after the feasibility trial and gave advice upon aspects of participant recruitment and follow-up for this definitive cRCT.

### Dissemination

Findings will contribute to the ongoing progression of the PACT programme of work. They will be disseminated widely to a broad audience including academics, clinicians, healthcare managers, policy makers, patients, the public, and participants within the study. The findings will be written up for publication in peer-reviewed journals and will be presented at national and international conferences, workshops and learning events.

## Discussion

Transitions from hospital to home can be risky, particularly for older people who often have complex health and social care needs [3]. Although limited, there is some evidence that interventions that support patient involvement offer a promising way to improve transitional care outcomes [12, 13]. The PACT programme of research therefore evaluates whether supported involvement of older patients and their families in hospital improves patient experience and safety at transitions of care. Through our earlier work [21, 24, 26, 27] we have designed an intervention that supports patients to ‘know more’ and ‘do more’ during their hospital stay so that they can manage their care at home post-discharge. The present study assesses the effectiveness and cost-effectiveness of this intervention through a cRCT. As with any complex intervention various challenges are anticipated throughout the study. The particular challenges of delivering this trial at this time (whilst health services are under sustained pressure during the COVID-19 pandemic) are outlined below.

### Recruitment and follow-up

The trial feasibility study was conducted in 2019/2020, just prior to the COVID-19 pandemic. Some of the targets for the trial were refined based on the findings from the trial feasibility study. For example, our estimates for attrition at follow-up, originally estimated at 10%, were adjusted to 25% based on the trial feasibility findings. As a consequence, our recruitment target increased from 20 to 25 patient participants per ward. We do not know what the impact of the pandemic will be on patients’ desire or ability to participate in research, particularly in this older population. Furthermore, we anticipate that increasing pressure on community services is likely to impact on recruitment and follow-up rates as patients who are medically fit for discharge to home are kept in hospital (acute or intermediate care) until care packages are available. Thus, our recruitment target might be extremely challenging to meet and might still underestimate attrition. We do not, however, anticipate any particular challenges to obtaining the routine data on readmissions.

### Contamination

In our trial feasibility study, we found that only one patient moved between an intervention and control ward. This suggested that our approach to minimise contamination, through recruiting wards that were not on the same care pathway, was successful. However, we know that since the start of the pandemic ward/bay closures are more frequent and there is a chance of more patient movement, and therefore greater contamination, between intervention and control wards than was experienced during the feasibility study.

### Implementation of the intervention

We anticipate that many of the contextual challenges that impacted the delivery of the intervention during the feasibility study will exist during the cRCT. The pandemic has undoubtedly placed additional stresses on our health services that are likely to impact on the capacity of staff to deliver the intervention. We know that a sizeable percentage of nurses have experienced burnout, post-traumatic stress disorder, and compassion fatigue (to patients and to each other) leading to staff absences [44–46]. Our intervention will necessarily create some additional work for staff, however, we hope that by asking them to reflect with empathy and compassion on patient involvement they will engage with YCNY [47].

## Trial status

This article refers to protocol version 9 dated 5/7/2021. Recruitment began on 8/11/2021 with completion expected by the end of March 2023. Post-discharge data collection is due to finish in May 2023. The study end date is October 2023 to allow for post-discharge data query clarification.

First submitted 19/01/23. Due to a processing error, resubmitted 25/7/23.

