**Methods:**

A multi-centre cluster randomised controlled trial (cRCT) will evaluate the effectiveness and cost-effectiveness of the YCNY intervention.

Forty acute hospital wards (clusters) in England from varying medical specialities will be randomised to deliver YCNY or care-as-usual on a 1:1 basis. The primary outcome will be unplanned hospital readmission rates within 30 days of discharge. This will be extracted from routinely collected data of at least 5440 patients (aged 75 years and older) discharged to their own homes during the 4- to 5-month YCNY intervention period. A nested cohort of up to 1000 patients will be recruited to the study to collect secondary outcomes via follow-up questionnaires at 5-, 30- and 90-day post-discharge. These will include measures of patient experience of transitions, patient-reported safety events, quality of life and healthcare resource use. Unplanned hospital readmission rates at 60 and 90 days of discharge will be collected from routine data.

A process evaluation (primarily interviews and observations with patients, carers and staff) will be conducted to understand the implementation of the intervention and the contextual factors that shape this, as well as the intervention’s underlying mechanisms of action. Fidelity of intervention delivery will also be assessed across all intervention wards.

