### Follow-up assessments (see the “ Outcomes” section above)

Following discharge from hospital, we will follow up recruited participants on control and intervention at three time points:Time 1 — post discharge: data collection will occur ideally between 5 and 17 days but up to a maximum of 21 daysTime 2 — 30 days post discharge: data collection will occur ideally between 30 and 45 daysTime 3 — 90 days post discharge: data collection will occur ideally between 90 and 105 days

At the point of recruitment, all participants will be advised that they will receive a questionnaire in the post and may receive a telephone call a few days later (as a reminder, to check receipt of the questionnaire or to offer support to complete). For participants who do not return questionnaires, a reminder will be sent out in the post and following this, one more reminder phone call will be made totalling up to four attempts to contact participants at each follow-up. Where contact is not made this will be recorded as missing data. Subsequent follow-ups will be initiated as planned. Researchers will not contact patients who have died since discharge.

If a patient loses capacity during the trial and therefore cannot complete the outcome measures, recruitment procedures will be followed to identify a personal consultee. Follow-up data will only be collected about participants who have lost capacity if the appropriate consent is in place. Participants will be given an unconditional £5 voucher at each follow-up time point.

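### The stated end of post-discharge data collection (May 2023) does not fit 90-day follow-up if recruitment runs to the end of March 2023; Time 3 questionnaires of the last recruits are exposed.

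*Protocol article*

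**What the plan says.** The calendar is given in the protocol article under Trial status: "Recruitment began on 8/11/2021 with completion expected by the end of March 2023". The next sentence reads "Post-discharge data collection is due to finish in May 2023", and the one after it "The study end date is October 2023 to allow for post-discharge data query clarification". The months between May and October are therefore assigned to data queries; no follow-up is assigned to them.

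The schedule is in the Follow-up assessments section. The clock starts at discharge and not at consent: "Following discharge from hospital, we will follow up recruited participants on control and intervention at three time points". The third is "90 days post discharge: data collection will occur ideally between 90 and 105 days". Nothing in the article shortens follow-up for patients recruited late.

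The 90-day data come from two sources. EQ5D-5L and patient-reported resource use come from questionnaires (Cost-effectiveness analysis section). Readmissions come from hospital records: "Unplanned hospital readmission rates at 60 and 90 days of discharge will be collected from routine data" (Abstract, Methods). They enter the main model, where "The outcome will be readmission (yes/no) at 30, 60 and 90 days" (Statistical analysis section).

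**The concern.** About two months separate the expected end of recruitment from the stated end of post-discharge collection, while the last scheduled contact is three months or more after discharge. Taken at their latest, the two dates leave room for the 30-day and 60-day points but not for the 90-day point.

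At stake is the last questionnaire of the nested cohort. It supplies the final EQ5D-5L for the QALY calculation and the final patient-reported resource use. The loss would not be spread evenly. The Recruitment and consent section says that start dates vary by Trust and ward and that each ward recruits for about four to five months, so missing Time 3 data would be concentrated in the wards that opened last. With 40 randomised wards, clustered loss of this kind need not balance between the arms.

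**Working it through.** **Inputs**
- Recruitment: 8 November 2021 to 31 March 2023, the latest reading of the stated forecast (Trial status).
- End of post-discharge collection: 31 May 2023, the most generous reading of May (Trial status). An earlier day in May makes the gap larger.
- Time 2 window: days 30 to 45 after discharge. Time 3 window: days 90 to 105 (Follow-up assessments).
- Readmission time points: 30, 60 and 90 days (Statistical analysis).
- Nested cohort: up to 1000 patients, 25 per ward (Abstract; Patient population and sample size).

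**Step 1. Forward from the last possible recruitment date.** Take a patient recruited and discharged on 31 March 2023. A patient still in hospital at recruitment is later on every line.

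| Days after discharge | Date reached | By 31 May 2023? |
|---|---|---|
| 30 | 30 April | yes |
| 45 | 15 May | yes |
| 60 | 30 May | yes |
| 90 | 29 June | no, 29 days late |
| 105 | 14 July | no, 44 days late |

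The stated May finish can be reproduced with follow-up to 30, 45 or 60 days. It cannot be reproduced with follow-up to 90 days.

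**Step 2. Backward from the end of collection.** 31 May 2023 − 90 days = 2 March 2023. Anyone discharged after 2 March has not reached day 90 by 31 May.

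**Step 3. Share affected.** From 8 November 2021 to 31 March 2023 is 508 days. Discharges from 3 to 31 March cover 29 days, and 29 / 508 = 5.7%. If discharges of nested participants are spread evenly over the period, 0.057 × 1000 ≈ 57 patients. The article gives no accrual curve, so the number is higher if recruitment is back-loaded and lower if it tapers off.

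**Step 4. Concentration by ward.** For a ward that recruits until 31 March over an assumed 120 to 150 days (four to five months), 29 days is 29/150 = 19% to 29/120 = 24% of its recruiting time. At 25 patients per ward that is 0.19 × 25 ≈ 5 to 0.24 × 25 = 6 patients. A ward that closed before March loses none, apart from patients discharged after 2 March.

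**The case against.** The strongest reply is that the recruitment date is a forecast of the latest finish, in an article first submitted on 19 January 2023. If the last discharge fell on or before 2 March, every patient reached day 90 by 31 May and nothing was lost. This stands, and it makes the point conditional. It does not remove it, because the article gives no last discharge date and no rule for late recruits.

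A reader might infer that 90-day readmissions are cut off as well. The documents do not support that. These come from dated routine records, which can be extracted in retrospect. Day 90 for a 31 March discharge is 29 June, well before the October study end, and the Discussion expects no particular difficulty in obtaining these data. The article does not promise an extract after May, but neither does it say that routine data stop then.

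A reader might also count everyone without a complete window to day 105, that is, discharges after 15 February (31 May − 105 days): 44 / 508 = 8.7%, or about 87 patients. This overstates the loss. Those discharged from 16 February to 2 March do reach day 90 by 31 May, and the window is stated only as an ideal. They have less time to respond, but their outcome is not lost.

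Nor can the loss simply be added to the 25% attrition in the sample size section. That allowance belongs to the PACT-M calculation, and the article text does not say at which time points PACT-M is collected.

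Finally, a date in a status note may be a reporting slip. The methods sections keep 90-day follow-up for all recruited participants, so the documents do not show that truncation was planned.

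**Conclusion.** The point holds as a conditional inconsistency of dates. With recruitment to the end of March 2023, the last recruits reach day 90 on 29 June at the earliest, and the ideal window closes on 14 July; both fall after the stated May finish. The exposed data are the Time 3 questionnaires of patients discharged after 2 March 2023: about 5.7%, or 57 of 1000, and up to about 19% to 24% of recruiting time in a ward that recruits to the last day. The figures rest on reading both dates at their latest, on even accrual for the overall share, and on 120 to 150 recruiting days for the ward share.

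The 30-day primary outcome is unaffected: day 30 falls on 30 April. The 90-day readmission comparison is safe provided that the extract is taken after the last patient's day 90. What remains concerns secondary questionnaire outcomes and the economic analysis. It is worth correcting because following the stated dates literally would lose data that the schedule requires, in the late-opening wards.

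**What to change.** Reconcile the three dates under Trial status with the follow-up schedule. State the actual or expected last discharge date, and let post-discharge collection and the routine-data extract both run to at least that date plus 90 days, ideally plus 105 (mid-July 2023 for a 31 March discharge). This fits inside the October 2023 study end. The cost is about six more weeks of questionnaires and reminders for the last recruits (44 days from 31 May to 14 July) and a later extract.

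The article was resubmitted on 25 July 2023, so this time may already have passed. In that case there are two possibilities. If follow-up did continue to day 90 for everyone, correct the stated finish date. If it stopped in May, report by arm and ward how many late recruits had truncated Time 3 follow-up, and treat them as administratively censored in the 90-day and cost-effectiveness analyses, separately from non-response. Either needs only a sentence or a short table. The article should also give the date of the routine-data extract, so that a reader can see that 90-day readmissions are complete.
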